### Sample size

To our knowledge, at the start of the study on 1 February 2017, no previous study had measured the efficacy of DT using the NPI-NH score. Therefore, a referral upon existing data could not be used in the power calculation. The power analysis was conducted using an estimated medium effect size (*f* = 0.25), an alpha level of 0.05, and a power of 0.8. According to statistical computing, a sample size of *n* = 128 is required, with 64 participants per group, for an analysis of covariance that includes the NPI-NH baseline score as a covariate. We planned an increase in sample size of 13 participants, because the expected drop-out rate is 10% due to possible acute clinical conditions interfering with the participation in the study, or death. In case of a refusal of the object (doll or cube), another participant will be enrolled as a replacement. Participants who underwent less than 60% of sessions will be excluded from analysis. The power calculation was performed with the programme *G*Power* 3.1 [27].

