**Methods/design:**

This single-blind, randomised controlled trial will involve people with dementia living in nursing homes of the Canton Ticino (Switzerland). Participants will be randomised to one of two interventions: Doll Therapy Intervention or Sham Intervention with a non-anthropomorphic object, using a 1:1 allocation ratio. The two interventions will consist of 30 daily sessions lasting an hour at most, led by a trained nurse for an hour at most. We will enrol 64 participants per group, according to power analysis using an estimated medium effect size (*f* = 0.25), an alpha level of 0.05, and a power of 0.8. The primary goal is to test the efficacy of the Doll Therapy Intervention versus the Sham Intervention as the net change in the following measures from baseline to 30 days (blinded outcomes): the Neuropsychiatric Inventory-Nursing Home administered by a trained psychologist blinded to group assignment, the professional caregivers’ perceived stress scale of the Neuropsychiatric Inventory-Nursing Home, patients’ physiological indices of stress (salivary cortisol, blood pressure and heart rate) and interactive behaviours. The secondary goal is to assess the relationship between attachment styles of people with dementia (detected by means of the Adult Attachment Interview to the patients’ offspring) and their caregiving behaviours shown during the Doll Therapy Intervention.

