### Randomisation and blinding

Participants will be assigned using a 1:1 concealed randomisation. The block randomisation will be computer based [28] and performed by an independent statistician. The statistician will generate the randomisation sequence and forward it to the study coordinator who will receive the randomisation for the allocation of the patients to either group A or B (block size: 2 × 2 = 4). To ensure blinding, the psychologist who administers the NPI-NH is not aware of the arm to which the participants belong. Conversely, the enrolled participants and the nurse are not be blinded with respect of the objects provided.

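### The abstract and the Sample size section give different enrolment targets (128 and 141); enrolling only 128 would leave about 115 analysed and power of about 0.76, not 0.80

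*Protocol article*

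**What the plan says.** The Sample size section takes a medium effect (f = 0.25) with "an alpha level of 0.05, and a power of 0.8" and concludes that "a sample size of *n* = 128 is required, with 64 participants per group". The test behind this figure is an ANCOVA whose single covariate is baseline NPI-NH. The section then makes an allowance for loss: "We planned an increase in sample size of 13 participants, because the expected drop-out rate is 10" (per cent). It attributes that loss to acute clinical conditions or death. Participants who refuse the doll or cube are to be replaced. A separate sentence adds "Participants who underwent less than 60% of sessions will be excluded from analysis".

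The abstract, under Methods/design, states the enrolment as "We will enrol 64 participants per group, according to power analysis".

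The Statistical analyses section says that efficacy will be analysed per protocol with all drop-outs excluded. The Trial status section says recruitment is still under way.

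**The concern.** The same figure, 64 per group, has two roles. In the Sample size section it is the number the ANCOVA needs, and 13 more are planned on top of it. In the abstract it is the number to be enrolled. The two agree only if nobody drops out, and the article itself expects 10% to do so.

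The total of 141 is never written out, so 64 per group is the only per-group figure a reader finds. If recruitment stopped there, the per-protocol analysis would rest on fewer participants than the power calculation requires. The way the 13 was obtained also needs checking, because a loss rate applies to those enrolled and not to those analysed.

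**Working it through.** **Inputs.** From the Sample size section: f = 0.25, alpha = 0.05, target power 0.80, two groups, one covariate (baseline NPI-NH), 128 required, 10% drop-out, 13 added. From the abstract: 64 enrolled per group, so 2 × 64 = 128. From Statistical analyses: drop-outs are not analysed.

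**Formula.** Power of the ANCOVA F test from the noncentral F distribution, with df1 = 1, df2 = N − 3 (two groups and one covariate) and noncentrality λ = f² × N = 0.0625 × N, where N is the number analysed.

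**Step 1: the article's own figure.** At N = 128, λ = 8.0 and df2 = 125, which gives power 0.801. At N = 127 power is 0.798. The smallest N that reaches 0.80 is therefore 128, and the stated requirement reproduces.

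**Step 2: where the 13 comes from.** 128 × 0.10 = 12.8, rounded up to 13. Equivalently, 128 × 1.10 = 140.8, rounded up to 141. This takes 10% of the analysed number. To have 128 left after losing 10% of those enrolled, the sum is 128 / 0.90 = 142.2, so 143, an addition of 15.

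**Step 3: what each enrolment figure delivers after 10% loss.**

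| Enrolled | Source | Expected analysed | Power |
|---|---|---|---|
| 128 | Abstract | 128 × 0.90 = 115.2 | 0.758 (0.757 at N = 115) |
| 141 | Sample size section (128 + 13) | 141 × 0.90 = 126.9 | 0.798 |
| 143 | 128 / 0.90, rounded up | 143 × 0.90 = 128.7 | at least 0.801 |
| 144 | 72 per group | 144 × 0.90 = 129.6 | at least 0.804 |

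The last two rows give power at the whole number below the expected count (N = 128 and N = 129).

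**Step 4: size of each effect.** Against 0.801 at N = 128, the abstract's target costs 0.801 − 0.758 = 0.043, about 4 percentage points. The multiply-up slip costs 0.801 − 0.798 = 0.003, about 0.3 of a point and about one participant.

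**The case against.** The best defence is that the abstract condenses. It reports the output of the power calculation, and the section devoted to sample size states the planned increase openly. On that reading the trial is aiming for 141, and the 0.76 arises only for someone who ignores the planned increase. This has force: nothing in the article says recruitment will stop at 128. It does not remove the conflict, because the abstract says how many will be enrolled and the number differs from the one the body implies.

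A second defence is that the 13-versus-15 slip does not matter. That stands. The effect size is a conventional value, chosen because no earlier NPI-NH data existed, and lowering f from 0.25 to 0.24 at N = 128 takes power from 0.801 to 0.769, about ten times the effect of the slip. A reader might infer that the miscalculated allowance by itself forfeits the stated power; the figures do not support that.

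Two other inferences are tempting and should not be drawn:

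- **141 is odd, so it breaks 1:1 allocation.** With "block size: 2 × 2 = 4", a 71/70 split or an incomplete last block is routine, and 143 is odd too.
- **The under-60% exclusion pushes power further down by a known amount.** The article gives no rate for it. Acute illness, already counted in the 10%, is an obvious reason for missing sessions, so the two losses may overlap. Refusers are handled by replacement.

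Finally, the article appeared in the month the study was expected to finish, so a few more participants would change little. That limits the value of raising the target, but not of stating which target applied.

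**Conclusion.** The point holds as an inconsistency between two enrolment figures. If the abstract's 64 per group is the operative target, about 115 are analysed and power is about 0.76, roughly 4 points below the stated 0.80. If the Sample size section's implied 141 is operative, about 127 are analysed and power is 0.798, which meets the intention for practical purposes. The allowance formula is wrong but is a minor correction.

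The article therefore does not show that the trial is underpowered; it shows that a reader cannot tell from it which number will be enrolled, and that one of the two clearly misses the stated power.

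The figures assume f = 0.25, one covariate, a loss of exactly 10% of those enrolled, and no further exclusions. Any additional loss from the 60% rule would lower them by an amount that cannot be derived from the article.

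**What to change.** State a single enrolment target in the abstract and in the Sample size section, and write out the total. Either:

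- use 143, or 144 as 72 per group if equal arms and complete blocks are wanted, which retains 128 after 10% loss; or
- keep 141 or 128 and give the expected analysed number and power that go with it (about 127 and 0.798, or about 115 and 0.76).

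In the same place, say whether the 10% already includes participants excluded for attending under 60% of sessions. If it does not, give the expected rate and add it to the allowance.

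Restating the figures costs only a text correction. Correcting the target upward costs two or three participants beyond 141.

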### Randomisation and blinding

Participants will be assigned using a 1:1 concealed randomisation. The block randomisation will be computer based [28] and performed by an independent statistician. The statistician will generate the randomisation sequence and forward it to the study coordinator who will receive the randomisation for the allocation of the patients to either group A or B (block size: 2 × 2 = 4). To ensure blinding, the psychologist who administers the NPI-NH is not aware of the arm to which the participants belong. Conversely, the enrolled participants and the nurse are not be blinded with respect of the objects provided.

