### Ethical considerations

The study procedures are in accordance with the principles outlined in the Declaration of Helsinki of 1964 and the following amendments. The study protocol was submitted to, and approved by, the Swiss Ethics Committees on Research Involving Humans (Ref. no. CE3140 BASEC2016–01992). The recruitment phase is ongoing. Briefly, during recruitment of the participants we check the presence of the aforementioned inclusion and exclusion criteria in order to establish the eligibility of each patient. Then, the patients or their legal representative (families) will be asked to sign a written informed consent for the use of their personal data and will receive a concise and comprehensive briefing explaining the research objectives and methods of data processing.

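### The protocol calls its randomisation concealed, but the procedure it states does not secure concealment and leaves a risk of selection bias

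*Protocol article*

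**What the plan says.** All the main statements stand in one paragraph of the protocol article, under Randomisation and blinding.

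- The claim: "Participants will be assigned using a 1:1 concealed randomisation".
- Generation: "The block randomisation will be computer based [28] and performed by an independent statistician".
- Handling: once the list exists, the statistician's next step is to "forward it to the study coordinator who will receive the randomisation for the allocation of the patients to either group A or B".
- Size of the blocks: a single one, "block size: 2 × 2 = 4".
- Blinding: "the psychologist who administers the NPI-NH is not aware of the arm to which the participants belong", whereas "the enrolled participants and the nurse are not be blinded with respect of the objects provided".

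On who enrols, the section Ethical considerations says only that "during recruitment of the participants we check the presence of the aforementioned inclusion and exclusion criteria"; no role is named. The Sample size section adds that a participant who refuses the doll or cube is replaced by another, without saying which allocation the replacement receives. Participants and setting gives 22 nursing homes. Nothing says whether one list serves all of them or each home has its own.

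**The concern.** Concealment depends on who can see the next assignment before an enrolment is final. It does not depend on who generated the list. An independent statistician protects the generation step, but once the sequence passes to a member of the study team that protection ends unless the holder is kept away from recruitment. The article describes its own mechanism here, and that mechanism does not support the word it uses.

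Two features add to the exposure. Delivery is open, so coding the arms as A and B hides little after the first session. A fixed block of 4 also makes later places in a block predictable to anyone who knows the earlier ones.

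If residents were approached, deferred or judged ineligible with the coming arm in view, the groups could differ in ways that bear on the NPI-NH comparison. Some eligibility criteria leave room for judgement, such as sitting comfortably or having an interfering acute condition. Adjustment for baseline NPI-NH and psychopharmacological therapy would remove only part of such a difference. Expected receptiveness to a doll, for example, is not among the covariates. Blinding the psychologist protects the assessment, not the selection.

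**Working it through.** **Inputs.** Block size 4 and 1:1 ratio (Randomisation and blinding). Planned enrolment 128 + 13 = 141 (Sample size). 22 homes (Participants and setting). The protocol gives no predictability figure to reproduce, and this point does not alter its sample size.

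**1. A person holding the sequence.** Every upcoming arm is known: 100%.

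**2. A person without the sequence who knows the block size and every earlier allocation in order.** There are 6 equally likely blocks of two A and two B, so 6 × 4 = 24 positions. The best guess is the arm with more places left in the block.

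| Position in block | Certain in advance | Correct guess |
|---|---|---|
| 1 | 0 of 6 | 1/2 |
| 2 | 0 of 6 | 2/3 |
| 3 | 2 of 6 | 2/3 |
| 4 | 6 of 6 | 1 |

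- Certain: (0 + 0 + 2 + 6)/24 = 8/24 = 33.3%. Over the trial, 141 × 1/3 = 47 allocations.
- Correct guesses: (1/2 + 2/3 + 2/3 + 1)/4 = 17/24 = 70.8%, against 50% by chance.

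At position 3 a guess is certain when the first two allocations are alike (2 of 6 blocks) and is even odds otherwise: 1/3 × 1 + 2/3 × 1/2 = 2/3.

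**3. Staff in one home.** The average is 141/22, about 6.4 participants per home. With one list across all homes, a home sees only scattered members of each block, so the figures in step 2 are upper bounds for its staff. With a separate list per home they would apply in full. The document does not say which holds.

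**4. Effect of varying the block size.** The sizes 4, 6 and 8 were drawn at random with equal probability and 141 allocations were simulated repeatedly. The observer was assumed to know the set of possible sizes but not the order in which they were used.

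| Scheme | Certain | Correct guess |
|---|---|---|
| Fixed 4 | 33% | 71% |
| Mixed 4, 6, 8 | about 2% | about 68% |

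Varying the size nearly removes certainty but lowers the guess rate by only about 3 percentage points. It does nothing against someone who holds the list. Withholding the sequence therefore matters more than changing the blocks.

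**The case against.** A reader might infer that allocation was in fact not concealed and that enrolment was steered by arm. The document does not support that. It gives the coordinator a role in allocating, not in recruiting. A central allocator whose list is invisible to those who screen and obtain consent is compatible with concealment. The text also does not say when, or in what form, the sequence is forwarded. This objection stands, and it limits the point to a risk that the stated procedure leaves open.

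It can also be said that a journal article may leave the release mechanism and the separation of roles to the full protocol. That is fair for what is merely unstated. It does not reach what is stated: the word concealed is used, and the described route takes the sequence to the study team.

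Further limits also stand:

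- The 33% and 71% need an observer who follows the whole trial in order without holding the list. No such person is identified.
- Reuse of a refuser's slot, which would make the replacement's arm known beforehand, is a possibility and not something the text says.
- That the block size appears in print adds little, since the article came out on 3 February 2020 and the trial was due to finish that month. Any exposure lies in what the team already knew.
- No bias in the NPI-NH has been measured.

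**Conclusion.** The point holds as a gap between claim and procedure. The protocol describes concealed randomisation, but forwarding the sequence to the coordinator who allocates, with a fixed block of 4 and open delivery, does not secure it. A breach is not shown.

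The size depends on who is looking. It is 100% foresight for a holder of the sequence. For an outsider who sees all earlier allocations it is at most 33% certain and 71% guessable, and for home staff it is less under a single list. These figures measure predictability. They do not estimate bias in the treatment effect.

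Whether the risk became real rests on one unstated fact: whether the holder of the sequence, or anyone with access to it, influenced screening, consent or order of enrolment. If that person was separate from recruitment and released arms only after enrolment was final, one sentence saying so would settle the matter.

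**What to change.** For all remaining enrolments:

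1. The independent statistician keeps the sequence and releases one allocation at a time, only after consent, eligibility and the baseline NPI-NH have been recorded.
2. A replacement for a participant who refuses the object takes the next unused allocation, never the vacated one.
3. As a secondary measure, the statistician regenerates the remaining list with randomly varying block sizes that are not disclosed to the study team.

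For enrolments already made, the report should say who held the sequence and whether that person took part in recruitment. If so, those allocations should not be called concealed.

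The cost is small: about one message to the statistician per participant and, for the third step, a new list for the remaining places with a slightly larger possible imbalance at its end. The sample size does not change. Because recruitment was due to end in the month of publication, few enrolments may remain, and the disclosure in the report may then be the more useful part.

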### Description of interventions

Participants will be randomly assigned to an experimental DTI group or to an active control group with SI. They will start the intervention within a week after randomisation. We chose to adopt an active control group instead of a no-treatment one to ensure comparability of experimental and control participants with respect to the efficacy of the intervention. Each participant will undergo daily sessions of DTI or SI*,* lasting an hour at most, led by a trained professional caregiver. Although the experimental phase of the study will be over, participants involved in DTI will continue to receive the doll, while participants involved in SI will start DT. The DTI involves the presentation of a doll produced by a Swedish brand and conceived for DT use. It is designed to recreate the sensation of touching, looking and holding a child in the arms. The SI group will attend similar daily sessions, but in place of the doll, it will be presented with a non-anthropomorphic object (i.e. a soft foam-rubber cube covered with a coloured and velvety textile) (Fig. 2).

**Fig. 2 Fig2:**
[figure not shown]
The doll and the soft cube

The first and 30th sessions of all participants will be videotaped by a trained psychologist as described below.

All sessions (DTI and SI) will take place inside the residential complex in a room known to the patient, with a bed and a chair on which the participant will sit; the only people in the room will be a nurse and the researcher who handles video-recording. The latter will never interact with patients and will stand behind a closet outside their field of view.

The object (doll or cube) presentation procedure will be structured in five standard steps as follows:
The nurse will accompany the patient in the room and the patient will take a seatThe nurse will then leave the room and return with the doll or the cube. The nurse will put the doll or the cube in front of the patient and will say ‘Good morning Mrs....look.’ The nurse will gaze at the patient. The tone of voice will be quiet. The doll or the cube will be shown in the same way: they will be held with both arms in front of the patient and away from the operator’s body. If the patient will not take the doll or the cube at the first attempt, the nurse will sit down in front of her holding the object in the arms and will wait for 2 mins. The nurse will invite the PWD again by saying ‘Take it’ and ‘It is for you’. If the patient will not take the object after the second request, the nurse will not insist, she will leave and say: ‘I have to go, goodbye Mrs....’. If the object is taken, the nurse will not comment in any way and will not interact with the patientShe will leave the patient and say ‘I have to go, goodbye Mrs....’. During this procedure the gaze will always be upon the patientInteraction with the object lasts 3 min starting from the moment when the nurse leaves the room. This phase is interrupted if the patient drops the object before the time limitThe nurse returns to the room and takes back the object

This procedure is based on the pilot study conducted by Pezzati et al. (2014) on ten residents of a special care unit for Alzheimer’s disease. The study has provided data supporting the feasibility and utility of the DTI in promoting well-being in patients with an advanced stage of dementia. The procedure is structured with the goal of recreating a situation of separation from a known figure and interaction with the environment in order to partially recreate the prototypical phases of the ‘strange situation’ [19]. The procedure has been simplified and adapted in order to make it administrable to institutionalised PWD and to highlight interactions with the offered items. All videotaped sessions will be analysed by the same evaluator, a trained psychologist who will fill the observational grids specifically developed for this study (see Tables 1 and 2). All participants will be assessed on the first day and the 30th day in the two groups (DTI and SI).

**Table 1 Tab1:** Observational grid for caregiving behaviours of the person with dementia (PWD) during the object presentation (doll or cube) (fulfill after the 1st and the 30th session looking at the videotape)

Patient ID:	Date:	1st session:	30th session:
*Doll Therapy Intervention*:	*Sham Intervention (cube)*:		
	Presence	Absence	
1.Object presentation			
*1.a.Gaze direction*:			
Toward the nurse			
Toward the object			
Between the nurse and the object			
Immediately toward elsewhere			
Between the nurse and the object, then toward elsewhere			
Other			
*1.b.Responses to the object presentation*:			
Acceptance			
Refusal			
Avoidance of the contact with the object			
Talking			
Asking the nurse for a meaning of the situation			
2. Separation from the nurse			
*2.a Responses to the separation from the nurse*:			
Acceptance			
Complain			
Worry			
Lack of interest			
3. Behaviours during the interaction with the object			
*3.a. Exploration behaviours*:			
Exploration behaviours			
Duration of exploration behaviours (seconds)			
Types of exploration behaviours			
Touching			
Smelling			
Looking at the object			
Moving the object around			
Relocating the object			
Other			
3*.b. Caregiving behaviours*:			
Caregiving behaviours			
Duration of caregiving behaviours (seconds)			
Types of caregiving behaviours			
Tightening grip on the object			
Caressing			
Cradling			
Talking			
Smiling			
Playing			
Other			
4.Separation from the object			
Putting the object aside			
After how long does the patient puts the object aside (seconds)			
Looking for the nurse			
Calling the nurse			
Staying seated			

*PWD* people with dementia

**Table 2 Tab2:** Observational grid for the situation of patient‘separation from the child (current attachment style of the person with dementia (PWD))

Patient ID:	Date:	
*Doll Therapy Intervention:*	*Sham Intervention (cube):*	
	Presence	Absence
*1. First stage: interaction between the patient and her child*		
*1.a. Gaze direction:*		
Toward the child		
Avoidant of the child		
Other		
*1.b. Responses to the interaction with the child:*		
Smiling		
Crying		
Seeking closeness		
Wandering		
Moving away from the child		
*2. Second stage: separation from the child*		
*2.a. Responses to the separation from the child:*		
Acceptance		
Complaining		
Worrying		
Lack of interest		
*3. Third stage: behaviours during the absence of the child*		
Crying		
Looking for the child		
Lack of interest		
Wandering		
Turning toward the stranger (the researcher)		
*4. Fourth stage: behaviours during the reunion with the child*		
*4.a. Gaze direction:*		
Toward the child		
Avoidant of the child		
Between the child and the room		
Other		
*4.b. Responses to the presence of the child:*		
Smiling		
Crying		
Screaming		
Seeking closeness		
Wandering		
Moving away from the child		
*NOTES:*		

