## Methods/design

### Primary goal

The primary goal of the present study is the 30-day efficacy of the Doll Therapy Intervention (DTI) versus a Sham Intervention (SI) on BPSD, professional caregivers’ perceived stress, patients’ physiological indices of stress, and interactive behaviours of PWD living in a nursing home. In particular, we expect an improvement in terms of a decrease in the Italian version of the Neuropsychiatric Inventory-Nursing Home total score (NPI-NH) [22, 23]. We also expect an improvement of professional caregivers’ perceived stress linked to BPSD of PWD in terms of a decrease in the NPI-NH Distress (NPI-NH-D) total score. Furthermore, we expect an improvement of the patients’ physiological indices of stress linked to their BPSD in terms of a decrease in the following parameters: salivary cortisol, blood pressure (systolic and diastolic) and heart rate, which are well-known biomarkers of acute stress. Finally, we expect an improvement of the patients’ interactive behaviours towards the object (doll) in terms of an increase in the number and duration of exploratory and caregiving behaviours.

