#### Interaction with the object outcome

We expect an increase of the interaction with the object (doll or cube), as exploration and caregiving behaviours during the object presentation. These measures will be recorded at the first and the 30th sessions by a trained psychologist who will fill an observational grid. It is a non-validated instrument developed for the aims of the present study that includes four areas related to different kinds of behavioural responses in a dichotomous way (behaviour: present/absent; see Table 1): object presentation, separation from the nurse, behaviours during the interaction with the object and separation from the object. We expect a significant difference in frequency of the interactions with the object from the first to the 30th session between the experimental and control groups.

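### Interaction with the object is a primary outcome labelled blinded, yet one evaluator scores it on a non-validated form showing session and object; masking the session would cheaply limit expectation bias

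*Protocol article*

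**What the plan says.** - Scoring (Description of interventions): "All videotaped sessions will be analysed by the same evaluator, a trained psychologist who will fill the observational grids specifically developed for this study". The caption of Table 1 gives the timing: "fulfill after the 1st and the 30th session looking at the videotape". The printed header of that form has fields for patient ID, date, 1st session, 30th session, doll and cube.
- Instrument (Interaction with the object outcome, under Primary outcomes): "It is a non-validated instrument developed for the aims of the present study". Most items are present/absent; exploration and caregiving also have durations in seconds.
- Expected direction (Primary goal): improvement is defined "in terms of an increase in the number and duration of exploratory and caregiving behaviours". The section on the interaction outcome expects the arms to differ in how interaction changes between the first and the 30th session.
- Blinding (Randomisation and blinding): "To ensure blinding, the psychologist who administers the NPI-NH is not aware of the arm to which the participants belong". No other assessor is described as blinded.
- Label (Abstract): efficacy is to be tested "as the net change in the following measures from baseline to 30 days (blinded outcomes"), and the list that follows includes interactive behaviours.

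**The concern.** A rater who knows both the object and the session has the two facts needed to score in the hoped-for direction. The object is visible on the tape and cannot be masked. Session number is different: room, script and objects are standardised, so much of what identifies the session comes from the form and the order of scoring, both of which the trial controls.

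Session is the right target because the stated contrast is a change. If the rater does not know the session, leniency towards the doll falls on both tapes of a resident and largely drops out of the difference. If the rater knows it, leniency can fall more heavily on the 30th-session tape, and it then stays in the contrast.

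There is room for judgement. The evaluator must separate exploration (touching, moving the object) from caregiving (caressing, playing, a tighter grip), and the recorded durations depend on that sorting. With a single evaluator, no second score would reveal drift. At stake is whether a significant result on this outcome reflects the residents or the scoring. The abstract tells readers that the outcome is blinded.

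**Working it through.** **1. The plan's own figure.** Inputs from Sample size: f = 0.25, two-sided alpha 0.05, power 0.80, ANCOVA with two groups and one covariate. The noncentrality is λ = f² × N = 0.0625 × 128 = 8.0, with 1 and 125 degrees of freedom. Power is 0.801 at N = 128 and 0.798 at N = 127. The stated 128 (64 per group) is reproduced, and this point does not contest it.

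**2. Is the blinded label supported?**
- The abstract counts interactive behaviours among blinded outcomes.
- The Randomisation and blinding section masks only the psychologist who administers the NPI-NH.
- The tape shows the object, and the grid header has fields for object and session.

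For arm, the label cannot be right. For session, nothing in the article supports it.

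**3. Illustration of an unmasked session.** Assume no true effect, 64 per arm, and a scoring shift of b SD of the change score in the doll arm beyond any shift in the cube arm. The documents give no value for b. The noncentrality is δ = b × √(64/2) = 5.657 × b; the two-sided critical value on 125 degrees of freedom is 1.979.

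| b (assumed) | δ | P(p < 0.05) |
|---|---|---|
| 0 | 0 | 5.0% |
| 0.1 | 0.566 | 8.7% |
| 0.2 | 1.131 | 20.2% |
| 0.3 | 1.697 | 39.1% |

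**4. What masking the session achieves depends on the analysis.** Suppose the session is masked and the doll arm gets the same leniency b, now in SD of a single score, on both tapes.
- *Change score:* bias = b − b = 0, so the rate is 5% if masking is perfect and leniency constant.
- *30th-session score adjusted for the first-session grid score*, with correlation ρ between sessions: bias = b(1 − ρ), residual SD = √(1 − ρ²). For assumed b = 0.2:
  - ρ = 0.3: 0.14/0.954 = 0.147, rate 13%
  - ρ = 0.5: 0.10/0.866 = 0.115, rate 10%
  - ρ = 0.7: 0.06/0.714 = 0.084, rate 8%
- *30th-session score adjusted only for baseline NPI-NH:* nothing cancels. The bias stays b, and at b = 0.2 the rate is about 20% if that covariate explains little of the grid score.

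The Statistical analyses section plans an ANCOVA of the primary outcomes and names baseline NPI-NH and psychopharmacological therapy as covariates, not the first-session grid score. The net-change wording in the abstract is the reading under which masking works best.

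**The case against.** - **Knowledge of session is inferred.** A reader might conclude that the evaluator certainly knows the session. No sentence says so. A record form needs identifiers, and the article does not say who fills in the header or when. The caption's timing also allows scoring after both tapes exist. An article may leave tape handling to the full protocol. This stands, and it limits the point to a risk. It does not remove the point, because the form is printed in full and the abstract claims blinding that the text does not support.
- **Expectation is not one-sided.** The section on the interaction outcome expects interaction to rise with doll or cube. Any common part cancels between arms; only the excess for the doll biases the contrast. This stands. An excess remains plausible, because the Primary goal section names the doll and a difference between arms is expected.
- **The error rates could be read as estimates.** They are not. The shifts are assumed, and a t-type calculation on a continuous change score only approximates a grid of mostly present/absent items. Timed durations and simple items leave less room for bias than a global rating would.
- **Masking could be read as a full and free cure.** Neither is supported. Step 4 shows that cancellation depends on the analysis, and dichotomous items and the three-minute limit on interaction prevent exact cancellation. A tape may also betray the session: a resident may ask what the object means when she first meets it. The text leaves open whether the psychologist who films also scores; if so, coding the tapes would achieve little. Tapes already scored would have to be scored again.

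**Conclusion.** The point holds as a risk that should be reduced. A directional primary outcome is scored by one evaluator on a non-validated grid whose header carries session and object. No masking of session is described, and the abstract calls the outcome blinded. Expectation of a larger rise with the doll can enter the contrast, by an amount the documents do not allow anyone to estimate. At 64 per arm, doll-specific shifts of 0.1 to 0.3 SD of the change score would give false-positive rates of about 9% to 39%. These rest on the assumed shifts, no true effect and a roughly continuous score.

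A reader might infer that the trial's main result is compromised. It is not: the section on the behavioural outcome calls the NPI-NH change the primary outcome, the sample size rests on it, and its assessor is masked to arm.

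**What to change.** 1. Remove date and session from the form the evaluator sees. The study coordinator gives each tape a random code and keeps the key.
2. Hold scoring until both tapes of a resident exist, then present tapes in random order across residents and sessions.
3. Have the tapes scored by a trained psychologist on the team who did not film them.
4. Re-link codes to sessions only after the grids are locked. Re-score under these conditions any tapes already scored.
5. State that this outcome is analysed as the change between the first and the 30th session, not as the 30th-session score adjusted only for baseline NPI-NH.
6. Drop the blinded label for this outcome, or limit it to masking of session.

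The cost is small: file coding, delayed scoring, separation of filming from scoring, and evaluator time for any rescoring. No extra residents or recordings are needed, and the sample size stays at 128.
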